### Healthy weight and anthropometric measurements

Participants will be classified according to WHO cutoff values for body mass index (BMI). Normal weight, overweight, obese and morbidly obese categories have a BMI of 18.5–24.9 kg/m^2^, 25–29.9 kg/m^2^, 30–34.9 kg/m^2^ and ≥ 35 kg/m^2^, respectively [41].

### Waist circumference

The waist circumference criteria used for diagnosis of abdominal obesity in the Arab and Middle Eastern population is ≥88 cm and ≥ 102 cm for women and men, respectively [37, 42].

### Behavioral change

As per the TTM [24], participants will be classified into five stages of changes (precontemplation (PC), contemplation (C), preparation, action, and maintenance) (Table 1) at the baseline visit and then every month during the first 6-month follow-up visit, through the WhatsApp application in the participants’ smartphones. This will test whether the sent messages were appropriate for the stage of behavioral change. This evaluation will be updated based on self-reported questions, which will be given to the participants separately and sent back to the research team through the WhatsApp application.

### Intervention

Interventions for this study will be on two levels. The standard health care, which is offered by primary health care services at King Saud University, Riyadh, Saudi Arabia and the text 4 change SMS messages.

### Message development

The content of the messages is derived from the WHO resources for a healthy diet, [31] physical activity and diabetes, Saudi National Diabetes Prevention and Control Program educational material [43], studies with similar interventions, online social listening, and clinical and personal experiences of Saudi culture [44]. The messages will be in formal Arabic with the infusion of some phrases and words from the common Saudi dialect. Messages are written in the second person, using you, your, and yours. Each stage of change of the TTM has a designated number of messages to promote a healthy diet and physical activity. The messages’ content was created according to the specific processes of change for each TTM stage. A total of 371 Arabic messages will be created by a health communication specialist and the project manager, who is well-acquainted with the target audience from a previous study. The specialist is well-acquainted with the Arabic speaking target population’s local accent, sentiments and culture. The messages’ content is based on international and national credible providers of health information and will be jointly prepared with a team of certified health educators. The messages will undergo cycles of feedback by a public health mental health specialist, a language reviser, and non-study participants from the target audience before the actual launch.

In the early stages of change (PC and C stages) that mainly require raising awareness, and contain nearly all essential messages needed to take the decision of change, every two messages are followed by a reminder, conveying the information mentioned in the previous messages every week (three for physical activity and three for a healthy diet). Reminders may take the form of text messages or multimedia messages (e.g. videos and infographics). For the following stages of change, where action is expected in the very near future or happening, the three weekly messages (for a healthy diet and physical activity) focus mainly on helping participants make a smooth transition through the process of change by providing a variety of messages conveying different alternatives of the same idea to achieve the goal of the stage.

The number of messages to cover 6 months are distributed as:

### Healthy diet messages

Healthy diet messages were 189 in total, distributed per stage as in precontemplation, contemplation, preparation, action and maintenance, 55, 48, 14, 60 and 12, respectively (Table 3).

**Table 3 Tab3:** Number of messages according to the stage of change

Healthy diet messages according to the stage of change						
^a^Stages of change as per ^b^TTM	Pre-contemplation	Contemplation	Preparation	Action	Maintenance	Total
Number of messages	55	48	14	60	12	189
Physical activity messages according to the stage of change						
Number of messages	56	51	14	60	12	193
Total	111	99	28	120	24	382

^a^For each stage, three messages about diet and three messages about physical activity will be sent every week

^b^TTM, Transtheoretical model of change

### Physical activity messages

For physical activity, a total of **193** messages were created to cover the stages of change, namely precontemplation, contemplation, preparation, action, and maintenance, 56, 51, 14, 60 and 12, respectively (Table 3). The content covers the different processes of change (such as consciousness raising, helping relationships etc.) as suitable for each stage of change.

### Length and delivery method of the messages

The SMS phone messaging will be done through the King Khalid University Hospital commercial delivery manager website (Easy SMS manager) and sent to participants three times per week during working hours. Messages will most probably be sent in the morning between 10 and 11 am. On each assigned day, they will receive two messages (one for physical activity and the other for diet) according to their stage of change. The easy SMS manager allows a message length of 70 Arabic language characters. If this limit is exceeded, it will be counted as two messages instead of one, thereby increasing the cost. The system uses a standardized communication protocol assuring the delivery of text messages to the participants; however, receiving text messages from the participants or exchanging messages is not permitted (i.e. it is a one-way system) To ensure that messages were delivered, they will also be sent to one of the authors’ smartphones. At every visit, each participant will be asked about the number of messages received to ensure that all messages have been delivered and seen.

### Time of messaging

The messages will be sent to the intervention group only in the first 6 months from the baseline. The following time points measure the intervention’s long-term effect on biological markers, and the stages of change for healthy eating and physical activity.

### Measuring the TTM stage of change, the effect of intervention in the long term

The TTM stage of change for physical activity and a healthy diet is determined at the baseline using a question adjunct to the WHO STEPS questionnaire. At the baseline visit and every month, the adjunct questions will be delivered to the participants’ smartphone through the WhatsApp application. This will detect progress in the stage of change and help us move on to the next set of messages accordingly. The WHO STEPS questionnaire will be administered at every 6-month follow-up visit to measure the interventions’ long-term effects on biological markers and changes towards a healthy diet and physical activity.

### Acceptance of the text 4 change SMS

At the first 6-month follow-up visit, we will assess the interventional messages using a specially designed questionnaire (adjunct questions). It will assess the user’s acceptance and satisfaction of the SMS program, using a scoring system from 0 to 10. It will assess the messages’ content, frequency, clarity and personal view of the impact of messages on the participants’ lifestyle. The list of questions also includes the preferred time to receive messages, and invites suggestions for improvement. A total score of 10 denotes that the text messages were highly accepted and satisfactory, and zero denotes that text messages were the least accepted and satisfactory.

### Pilot study

Prior to commencing the actual study, we will recruit 30 non-study participants for a pilot study to be conducted in 1 month. We will assess the questionnaire for face validity, feasibility, and an estimate of the time taken to administer the questionnaire. Participants will be asked for verbal feedback while completing the survey. The SMS messages will be sent, based on the stage of change for each participant to review (from 408 messages) and give feedback on the ease of language and content. We will keep a feedback log to track all needed changes for the questionnaire and text messages. In this one-month pilot study, we will test the electronic messaging system, the feasibility of remote follow-up, and the documentation and data management strategy. Data collected in this pilot study will be analyzed and published.

### Study outcomes

By the end of the trial, we expect the following outcomes:

#### Primary outcome

Adoption of healthy lifestyle behaviors including healthy eating and physical activity practices complying with WHO recommendations. Incidence of T2DM, based on a change in HbA1c with an expected reduction of 1–2% at the end of the trial.

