### Randomization and blinding

Recruited, eligible participants will be randomized into two groups (1:1 ratio), using random numbers table generated in the Statistical Package for Social Studies (SPSS v. 21) (SPSS v. 21, IBM Corp., New York, NY, USA) by an independent statistician. The laboratory staff, biostatistician, health educator, and principal investigator will be blinded to the participant’s group allocation until the end of the study. The participants will not be blinded to the intervention due to its nature, as well as the research assistant/project manager who is responsible for disseminating the text message intervention.

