#### Assessment of interventions

All participants will complete the WHO STEPS instrument version 3.1 at the baseline visit and during each follow-up visit. This will assess behavioral risk factors including healthy diet, physical activity and the participants’ behavioral change(s) stage based on the TTM at the baseline visit and follow-up visits for progression in the stages of change.

Data about adherence to physical activity and healthy dietary intake recommendations will be recorded at every 6-monthly follow-up visit. Adherence will be self-reported every 6 months and scored as poor, moderate or good. Physical activity and dietary intake will be categorized as adherent or nonadherent for statistical analysis.

At every visit after the baseline visit, we will assess the mobile messages in the intervention group through a specially designed questionnaire. It will assess the user acceptability and satisfaction of the SMS messages program using a scoring system of 0–10. It will assess message content, frequency, clarity, effect on personal life (“degree of disturbance”), and personal views of the impact of these messages on lifestyle. The list of questions also includes the preferred time to receive messages and invites suggestions for improvement. A maximum total score of 10 denotes that the text messages were highly acceptable and satisfactory, while the lowest score of zero denotes that the text messages were the least acceptable and unsatisfactory.

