#### Secondary outcomes at 6-month follow-up visits

Change in the TTM towards stages of action and maintenance, decreased levels of LDL-C to < 130 mg/dl or ≤ 5.1 mmol/l, change in the systolic\diastolic blood pressure to normal blood pressure < 120/80 mmHg, respectively, decrease in body weight by 5–10% per year, improvement in the physical activity level to the recommended 150 min per week and improvement in the daily consumption of portions of fruit and vegetables to 5–7 servings/day.

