### Data analysis plan

Data will be analyzed using the Statistical Package for Social Studies (SPSS 22; IBM Corp., New York, NY, USA). Continuous variables will be expressed as mean ± standard deviation or median and interquartile ranges according to the normality assessment. Categorical variables will be expressed as frequencies and percentages.

The chi-square statistical test will be applied for categorical variables to assess the association between them. The t-test or Mann-Whitney test will be used to compare numeric variables. Repeated measures analysis of variances or Friedman’s test will be used to evaluate repeated measures over the follow-up period.

The incidence rate and cumulative incidence rate will be computed for incidence of T2DM among the intervention and control groups. Additionally, comparison between the incidence of T2DM among different age groups and gender will be evaluated. Kaplan-Meier survival curves and log-rank tests will be used to compare the intervention and control groups as well as the different risk groups for progression to T2DM, and transition and/or relapses from different stages of TTM.

Hazards ratios with 95% confidence intervals will be calculated and the adjustment of known confounders will be adopted in the Cox regression model. In all the analyses, *P*-values < 0.05 will be considered statistically significant.

The principal analyses of primary and secondary outcomes will use the intent-to-treat approach. The intent-to-treat analyses will include all participants in their randomly assigned treatment groups regardless of a participant’s adherence to the assigned treatment regimen.

All data entry will be anonymous and identification numbers will be saved in a password-protected log file with the primary investigator. Backup of entered data will be created monthly to avoid any loss of collected data. An interim analysis of data will be conducted 12 months after recruitment of the last participants. Interim analysis aims to evaluate the completeness and accuracy of the collected data and early detection of any difficulties.

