### Sample size calculation

A sample size of 300 is required so that there are 150 participants each in the intervention and control groups. The sample size was calculated by using Stata® software version 15 (StataCorp, College Station, Texas, USA) with the assumptions that α = level of significance (0.05), β = Type II error (power of the study = 1- β = 80%). The hazard rate of diabetes development among the control group is 10% over the 2 years, the hazard rate of diabetes development among the intervention group is 7% over the 2 years (reduction of about 30%) and the minimum sample size required to reject the null hypothesis is 256 (128 in each group). With an expected loss of follow-up around 20%, the sample size was increased to 300 participants in total.

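### Behaviour adoption and T2DM incidence are both listed as primary, unranked and each tested at 0.05, with no rule on whether one or both must succeed

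*Protocol article*

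**What the plan says.** All references are to the protocol article.

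- **Primary outcome.** The first item is "Adoption of healthy lifestyle behaviors including healthy eating and physical activity practices complying with WHO recommendations". The second is "Incidence of T2DM, based on a change in HbA1c with an expected reduction of 1–2% at the end of the trial". No order, joint-success rule or division of alpha is given.
- **Data analysis plan.** "In all the analyses, *P*-values < 0.05 will be considered statistically significant".
- **Sample size calculation.** The only inputs are diabetes rates of 10% (control) and 7% (intervention) over 2 years, a significance level of 0.05 and 80% power. The minimum total is 256. No behavioural effect is assumed.
- **Primary objective.** The question is whether the messages prevent or postpone T2DM. Better diet and more activity are the means.
- **Secondary outcomes at 6-month follow-up visits.** The list includes "improvement in the physical activity level to the recommended 150 min per week" and a target of 5–7 daily servings of fruit and vegetables.
- **Assessment of interventions.** "Adherence will be self-reported every 6 months and scored as poor, moderate or good".
- **Randomization and blinding.** "The participants will not be blinded to the intervention due to its nature". Laboratory staff and the biostatistician are blinded.
- **Physical activity.** Steps are also counted by smartphone in the first week of each 6-month follow-up visit.

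**The concern.** With an unranked primary list and 0.05 for each test, the plan does not fix what counts as a positive trial. If either item is allowed to carry the conclusion, the error rate for that conclusion exceeds the nominal 5%.

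The two items also differ in how well they are protected. The T2DM outcome rests on a laboratory value from blinded staff. The behavioural outcome rests largely on what participants say about themselves, and only the intervention group has been sent messages recommending those behaviours. A difference in reporting could therefore produce a behavioural result without any effect on T2DM, which is what the primary objective asks about.

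The overlap with the secondary list adds to the ambiguity: a reader cannot tell whether a given activity result would be reported as primary or secondary.

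**Working it through.** **1. Which outcome and alpha the sample size reflects.** Inputs from the Sample size calculation: rates 0.10 and 0.07, alpha 0.05, power 80%. Sidedness is not stated. The exponential test on a difference of hazards, 1:1, two-sided, with every participant counted as an event, gives per arm

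n = [(1.960 × √(2 × 0.085²) + 0.842 × √(0.10² + 0.07²)) / 0.03]²
= [(0.2356 + 0.1027) / 0.03]² = 127.2, rounded up to 128, so 256 in total.

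This matches the article's figure. The one-sided version gives 202. The stated size is therefore consistent with a single two-sided test of T2DM at 0.05, with no allowance for a second primary outcome. Whether 256 is adequate is a separate question and is not used here.

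**2. Family-wise error if any one primary result suffices.** For k independent tests at 0.05, the error is 1 − 0.95^k.

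- k = 2 (behaviour as one outcome, plus T2DM): 1 − 0.9025 = 9.75%.
- k = 3 (eating, activity, T2DM): 1 − 0.857375 = 14.3%.

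**3. The same with correlated tests.** The documents give no correlation, so a range is assumed. Simulated normal test statistics with equal pairwise correlation (1,000,000 draws, two-sided 0.05 each) give:

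| Correlation | Two primaries | Three primaries |
|---|---|---|
| 0.3 | 9.5% | 13.7% |
| 0.5 | 9.1% | 12.5% |
| 0.8 | 7.8% | 9.8% |

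Every entry is above 5%.

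**4. If both must succeed.** The error rate does not exceed 5%, because a false claim requires the truly null component to cross 0.05. The article does not state this rule.

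**5. Overlap between tiers.**

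- Activity: the Physical activity section defines being active as 150 minutes of moderate activity per week, and the secondary list uses the same threshold. The overlap is close.
- Diet: the Healthy eating section covers salt, fibre, fast food, sweetened drinks and late snacks as well as fruit and vegetables. The secondary item covers only fruit and vegetables. The overlap is partial.
- Timing: the outcomes are introduced as expected by the end of the trial, while the secondary heading refers to the 6-month visits. The time points may differ.

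**The case against.** **Silence.** A journal article may leave hierarchy and alpha allocation to a fuller document, and a threshold per test is not a decision rule. A reader might infer that the plan permits success to be declared on behaviour alone. The article does not say so; it states neither an either-suffices nor a both-required rule. What remains is that it does positively set an unadjusted 0.05 for all analyses over an unranked primary list.

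**Number of tests.** The behavioural item can be read as one outcome, and behaviour and T2DM are likely to be correlated, since one is meant to act through the other. Three tests are not established, so 14.3% is an upper case and the two-test range is better supported.

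**Reporting bias.** The article openly says that participants cannot be blinded. Step counts mean that activity is not purely self-reported, and messages stop after 6 months of a three-year trial. This softens the concern. However, the adherence categories are self-reported, and the step counts are not named in either outcome list.

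**Choice of primary.** Behaviour is a legitimate endpoint for a behavioural intervention, and it is listed first. That is fair, but the objective and the sample size both point to T2DM.

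**A tempting stronger reading.** A reader might go on to infer that a positive trial would most likely rest on self-report because T2DM is underpowered. The documents do not support this. With 2-year risks of 10% and 7%, T2DM power is about 15% at 150 per arm but about 40% at 508 per arm. The article gives both 300 and 1,016 participants, and it assumes no behavioural effect with which to compare.

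**Conclusion.** The point holds in a limited form. The article lists at least two unranked primary outcomes, tests each at an unadjusted 0.05, and does not say whether one or both must succeed.

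If either suffices, family-wise error is about 8% to 10% for two primaries and at most 14.3% for three. These figures depend on the either-suffices reading and, below the independent values, on assumed correlations of 0.3 to 0.8. Under a both-must-succeed rule there is no inflation.

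The mismatch does not depend on those assumptions: the objective and the sample size concern T2DM alone, yet a largely self-reported behavioural outcome has equal rank. It would overstate matters to say that the same endpoints sit in both tiers. Activity is closely duplicated, diet only in part, and the time points may differ.

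**What to change.** Name incident T2DM as the single primary outcome, tested at two-sided 0.05. This matches the objective and leaves the alpha in the sample size unchanged. Keep diet and physical activity in the secondary list, and add the smartphone step counts as a supporting objective measure of activity.

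If the sponsor wants behaviour to remain primary, state a fixed sequence with T2DM tested first at 0.05 and behaviour tested only if T2DM is significant. Splitting alpha equally would also control the error, but by the article's own sample-size method it raises 256 to 308 for two primaries (0.025 each) or 340 for three (0.0167 each).

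The preferred change costs only wording, in the protocol and in the registry entry if that carries the same list. It needs no new data. The downside is that a result on behaviour alone could no longer be presented as a positive primary outcome.

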#### Secondary outcomes at 6-month follow-up visits

Change in the TTM towards stages of action and maintenance, decreased levels of LDL-C to < 130 mg/dl or ≤ 5.1 mmol/l, change in the systolic\diastolic blood pressure to normal blood pressure < 120/80 mmHg, respectively, decrease in body weight by 5–10% per year, improvement in the physical activity level to the recommended 150 min per week and improvement in the daily consumption of portions of fruit and vegetables to 5–7 servings/day.

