#### Physical measurements

At the baseline visit, all recruited participants’ weight, height, waist circumference, and blood pressure from the left arm will be measured in a sitting position, and the mean of two readings will be considered. Blood tests for HbA1c and lipid profiles will be performed by qualified laboratory personnel. Glycated hemoglobin (HbA1c) and fasting lipid profiles will be measured for all participants at baseline and at every 6-month follow-up visit.

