### Dyslipidemia

Subjects will be categorized as having any sort of dyslipidemia according to the WHO and the Third Adult Treatment Panel (ATP-III) of the National Cholesterol Education Program (NCEP). Dyslipidemia includes raised levels of total cholesterol, and/or low-density lipoprotein cholesterol (LDL-C), and/or triglycerides and low levels of high-density lipoprotein cholesterol (HDL-C), or if the subject reported using medications to lower blood lipid levels [36, 37].

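### The LDL-C target in the secondary outcomes is given as two figures that are not equivalent: 130 mg/dl is about 3.36 mmol/l, and 5.1 mmol/l is about 197 mg/dl

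*Protocol article*

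**What the plan says.** The protocol article's section headed "Secondary outcomes at 6-month follow-up visits" lists six items. The one on LDL-C reads "decreased levels of LDL-C to < 130 mg/dl or ≤ 5.1 mmol/l". It is the only lipid in that list.

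Three other sections bear on it:

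- **Physical measurements.** LDL-C will be available at every visit, because "fasting lipid profiles will be measured for all participants at baseline and at every 6-month follow-up visit". No reporting unit is given.
- **Dyslipidemia.** Raised LDL-C is named as a component of the definition, but no numerical limit is attached.
- **Data analysis plan.** Both kinds of variable are covered: "The chi-square statistical test will be applied for categorical variables to assess the association between them", and "The t-test or Mann-Whitney test will be used to compare numeric variables". The section does not say which approach LDL-C will receive.

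The article gives no other LDL-C cut-off and no conversion factor, and it does not say which of the two figures governs.

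**The concern.** Two figures in different units, joined by 'or', normally express one limit twice. Here they differ by far more than rounding could produce, so the outcome has no single definition.

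The item is worded as reaching a level, like the blood pressure item beside it. Counting participants at target and comparing the arms by chi-square is therefore a natural reading. On that reading, the count depends on which figure is used, and the question recurs at each six-monthly visit. If it is settled only once data are in hand, the definition of success for a named outcome is chosen after the fact.

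**Working it through.** **Inputs**

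- Target in conventional units: below 130 mg/dl (protocol article, secondary outcomes).
- Target in SI units: at or below 5.1 mmol/l (same line).
- Conversion factor: not in the document. It is derived here from the chemical formula of cholesterol, C27H46O. The molar mass is 27 × 12.011 + 46 × 1.008 + 15.999 = 386.66 g/mol. Dividing by 10 gives 38.67 mg/dl per mmol/l.

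**Step 1: try to reproduce the stated pair.** The formula is mmol/l = (mg/dl) / 38.67.

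- 130 / 38.67 = 3.36 mmol/l. The article has 5.1.
- 5.1 × 38.67 = 197.2 mg/dl. The article has 130.

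The stated pair is not reproduced in either direction.

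**Step 2: size of the gap.**

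- 197.2 − 130 = 67.2 mg/dl.
- 5.1 − 3.36 = 1.74 mmol/l.
- 197.2 / 130 = 1.52, so the second limit is about 52% higher than the first.

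**Step 3: could the factor explain it?**

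| Factor (mg/dl per mmol/l) | 130 mg/dl in mmol/l | 5.1 mmol/l in mg/dl |
|---|---|---|
| 38.0 | 3.42 | 193.8 |
| 38.67 | 3.36 | 197.2 |
| 39.0 | 3.33 | 198.9 |

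For the two figures to agree, the factor would have to be 130 / 5.1 = 25.5, which is far outside this range. Using another analyte's factor by mistake does not explain it either. The triglyceride factor (88.57) turns 130 mg/dl into 1.47 mmol/l, and the glucose factor (18.02) turns it into 7.22 mmol/l.

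**Step 4: consequence under each reading.**

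- *One cut-off in two units.* A participant with LDL-C of at least 130 and up to about 197 mg/dl (3.36 to 5.1 mmol/l) misses the target by the mg/dl figure and meets it by the mmol/l figure.
- *Either figure is enough.* Anyone below 130 mg/dl is also below about 197 mg/dl, so the first limit is redundant and the working target is about 197 mg/dl. Classification is then unambiguous, but half of the stated criterion has no function.

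These are alternative readings, and their consequences should not be added together.

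**Step 5: the operators.** One limit is strict and the other inclusive. Even with a correct conversion, a value exactly at the cut-off would be scored differently in the two units. This is a small point, but it sits in the same line.

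**The case against.** The strongest case on the other side accepts the arithmetic and contests the consequences.

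- **A threshold analysis is not fixed.** The outcomes are introduced as what the investigators expect to see. The secondary objective concerns biomarker levels, and the analysis section offers tests for numeric variables and repeated measures as well as chi-square. If LDL-C is compared as a numeric value, the faulty cut-off changes no result. This stands, and it makes the harm conditional.
- **Nothing central depends on it.** LDL-C is one of six secondary items. The primary outcome does not use it, eligibility does not use it, and the sample size rests on diabetes rates of 10% and 7%. This stands, and it limits the severity.

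A reader might also infer more than the document supports:

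- *That nearly everyone would meet the looser limit, leaving the outcome close to its ceiling in both arms.* This needs an LDL-C distribution for the trial population, and none is given. The number of participants between 130 and about 197 mg/dl is unknown.
- *That laboratories reporting in different units would give different results.* Recruitment and visits run through one institution, and nothing suggests more than one reporting unit. What can be said is only that the unit is not stated.
- *That LDL-C should therefore be analysed mainly as a continuous variable.* That is an analysis choice which does not follow from a conversion error, and it may be settled in an analysis plan that is not shown.

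None of this repairs the line itself. It is running prose with no sign of redaction or a broken table. The article does not leave the figure to a fuller document; it states the figure, and the two halves disagree.

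**Conclusion.** The point holds as an error in a stated threshold. The two LDL-C figures differ by about 67 mg/dl (1.74 mmol/l), the second being about 1.52 times the first. No plausible cholesterol factor closes the gap, and no other section resolves it.

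The only outside input is the conversion factor, taken from the molar mass of cholesterol. Varying it from 38.0 to 39.0 leaves the conclusion unchanged.

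The effect is confined to an analysis of LDL-C as a threshold outcome, and its size in participants cannot be estimated from the document. It would be wrong to read this as a threat to the trial's main conclusions, since neither the primary outcome nor the sample size involves the figure. Severity is minor to moderate: a definite mistake in a named secondary outcome, with limited reach.

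**What to change.** Before outcome data are analysed, reconcile the LDL-C item in the secondary outcomes to one cut-off, with one operator used in both units and an equivalent that matches arithmetically. The two consistent pairs are:

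- 130 mg/dl with 3.36 mmol/l; or
- 197 mg/dl with 5.1 mmol/l.

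The document does not show which figure was intended, so the investigators must say, and no choice is proposed here. It would help to state the laboratory's reporting unit in the same edit.

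The cost is a correction to one line. It needs no change to data collection, sample size or the planned tests.
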